#### Parent reported

Three different 100 mm Visual Analogue Scales (VAS) are used to evaluate the following outcomes:

Parent satisfaction with information (measured on the morning of surgery after arrival at the hospital).Parental anxiety: The VAS-parent anxiety (VAS-PA) is a rapid method of assessing self-reported anxiety levels of parents before surgery. It has been shown to correlate sufficiently with the State Trait Anxiety Inventory (STAI) (r=0.64, p<0.001), the gold-standard research tool used to measure adult state and trait anxiety.^28^ The VAS was chosen as our measure of parental anxiety rather than the STAI - a 40-point questionnaire taking 5–10 min to complete; this is because the STAI was observed in our phase 2 feasibility trial to lead to distress when given to parents/carers immediately following the observation of the induction of anaesthesia in their child. In comparison, the VAS-PA takes 30 s to 1 min to complete and is less likely to lead to distress.Parental satisfaction (VAS): found to be more sensitive to differences in levels of parent satisfaction when compared with a 20-point questionnaire used in the feasibility trial. Minimal differences were observed between trial arms, with the majority of participants parents/carers giving full marks in all 20 questions.

Prior to discharge home, parents/carers in both trial arms are also asked to complete a questionnaire assessing if they have used the VR headset and if they or their child developed any adverse symptoms through its use. Similarly, if the child was randomised to the intervention, we ask about any reasons for not using the LJ app.

Telephone consultations at 2 and 4 weeks after surgery ask the following information of parents/carers:

The Post-Hospital Behavioural Questionnaire,^29^ a validated measure assessing children’s behavioural changes following ambulatory surgery.Number of days worked missed by parent(s) or school missed by children, and the reasons including adverse behavioural effects. This provides discrete data and will be used to conduct a social cost analysis

### Independent observations

Independent observations are undertaken before and during induction of anaesthesia by the same observer who is recording the primary outcome, and who is blinded to treatment allocation.

Children’s compliance during induction: VAS-distress is measured through a 100 mm VAS by the independent observer immediately following observing the induction of anaesthesia (time point 3). This produces continuous data to analyse. No gold-standard tool available for both inhalation and intravenous inductions.Children’s distress during induction: VAS-compliance measured through a 100 mm VAS by the independent observer immediately following observing the induction of anaesthesia (time point 3). No gold-standard tool available.

#### Process measures

The case report form (CRF) includes data to be collected for the purpose of comparison between trial arms and description of care processes—these include: premedication (including anxiolysis and/or sedation); type of induction and maintenance of anaesthesia; pharmacological adjuncts (for anaesthesia, analgesia, antiemesis or other symptom control); time to recovery readiness; use of rescue analgesia and antiemetics; unplanned admissions, change in anaesthetic plan and failure to progress with surgery.

#### In-app analytics

For participants in the intervention arm, the app will record the number of times the application is used, including the number of animations triggered and timing of use.

### Data management

Data will be collected from sites using an eCRF (MACRO). Participants are given a unique study subject identifier and subject number.

### Trial end and closedown

A 3-month period for follow-up of patients who have been recruited and randomised will be provided after the date of the last participant recruited. Following that, and data validation, the trial database will be locked for analysis.

### Analysis plan

Data analysis will be overseen by GA as trial lead statistician. Trial arms will be labelled as groups A or B and a postdoctorate research assistant will perform the analysis of the use of the in-app analytics compared with primary outcome measure. Only this team of statisticians will have access to the final trial dataset prior to analysis.

The management of missing data, non-compliers and withdrawals is outlined further in the statistical analysis plan document.

### Primary outcome analysis

We will analyse using an intention-to-treat approach. Our primary analysis will compare mean mYPAS-SF scores at time point 3 (in the anaesthetic room before induction of anaesthesia) between study groups using a mixed-effects regression model with fixed effects for treatment and specialty, and a random effect for centre. All modelling assumptions will be checked, including the assumption of normality for both sets of residuals. If substantial departures from normality occur, then transformations of the outcomes will be considered to achieve normality (of the residuals). Participants who do not contribute any measurements for the primary outcome will be omitted from this analysis.

In addition, the m-YPAS-SF score at other time points will be analysed:

The mean score at time point 2 will be compared.The number of participants with a score >30 in either the standard care and intervention arms at time points 2 and 3 will be tabulated and compared.

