## Introduction

 Anxiety before an operation is common and has an impact. Over one-third of adult patients state that anxiety is the worst thing about having surgery, and it has a greater impact on patient experience than pain, postoperative nausea and vomiting and other symptoms.^1^ Anxiety affects between 50% and 75% of children on the day of surgery.^2^,^4^ Risk factors include the age of the child, personality traits such as low sociability and high impulsivity, parent anxiety, and previous negative healthcare experiences.^5^,^8^ Multiple studies in children have shown links between perioperative anxiety and poor compliance with induction of anaesthesia, emergence delirium and adverse postoperative outcomes such as poor wound healing, regressive behavioural changes and increased analgesic requirements.^29^,^12^

Emotion-focused coping techniques such as the use of distraction interventions (books, toys, clown doctors) and low-sensory environments have been shown to reduce children’s preoperative anxiety.^9 13 14^ Similarly, problem-focused coping techniques, such as preoperative education through hospital tours, information booklets and play therapy, have been shown to be effective when used in isolation or as combined interventions.^515^,^18^ More recently, advances in technology and their availability have meant that the use of smartphones and hand-held tablets is becoming increasingly popular methods of delivering emotion-focused and problem-focused coping interventions.^319^,^22^

The ubiquity of smartphones brings the opportunity to provide interactive and engaging information designed for children and their parents, delivered in their own home. The development of any new preoperative educational intervention should be tailored to the age and level of understanding of the child,^18 23^ delivered at a suitable time to allow for the information to be processed and coping strategies developed, depending on the age of the user,^24^ linked with parental information and provide children with information about each step of the hospital journey.^11^ The Little Journey (LJ) app was developed to support preoperative preparation in children between 3 and 12 years of age, adhering to these design principles.

This manuscript describes the protocol for a randomised controlled trial (RCT) to evaluate the clinical effectiveness of the LJ app at reducing anxiety in children undergoing surgery under general anaesthesia.

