### Inclusion criteria

Children aged between 3 and 12 years of age on the date of parental consent to participate in the trial.Those undergoing surgery planned to be conducted as a day case (surgery is defined as any therapeutic procedure taking place under the care of an anaesthetist and surgeon or dentist).Requiring general anaesthetic (must be their first general anaesthetic).Both the child and parent are able to speak/understand one of the languages available on the app.American Society of Anesthesiologists’ physical status class I–IIIClass I: A normal healthy patient.Class II: A patient with mild systemic disease.Class III: A patient with severe systemic disease.

Surgery is defined as any procedure occurring in a theatre under the care of a surgeon or dentist and an anaesthetist.

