### Randomisation

All eligible and consented participants will be randomised after baseline assessment to one of two arms. Randomisation is performed using Sealed Envelope, an online software application frequently used in clinical trials. Randomisation will use minimisation to ensure balance across study sites and three groupings of surgical procedures: ear, nose and throat, dental and maxillofacial; urology and gynaecology; and general surgery, orthopaedics and other procedures.

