#### Secondary outcomes

A combination of parent-reported, independently assessed and objective secondary outcomes are collected on the day of surgery and then at 2 and 4 weeks after surgery (table 2).

**Table 2 T2:** Outcome measurement schedule

	Study period						
	**Preassessment clinic**	**Day of surgery**				**Postdischarge**	
**Timepoint**	**T1**	**T2**	**T3**	**T4**	**T5**	**T6 (2 weeks)**	**T6 (4 weeks)**
Assessments							
Modified Yale Pre-operative anxiety scale- Short-form	**X**	**X**	**X**				
VAS-Parent Anxiety	**X**		**X**				
VAS-satisfaction with informatio		**X**					
VAS-compliance			**X**				
VAS distress			**X**				
Time to induction			**X**				
Analgesic use				**X**			
Antiemetic use				**X**			
Time to recovery				**X**			
VAS-parent satisfaction with care					**X**		
Adverse events questionnaire					**X**		
Time to discharge					**X**		
Unplanned admission					**X**		
Unplanned cancellations					**X**		
Post Hospital Behaviour Questionnaire						**X**	**X**
Number of days of work/school missed						**X**	**X**

VASVisual Analogue Scale

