#### Secondary outcome analysis

In general, for continuous secondary outcomes, we will perform analyses analogous to the analysis of the primary outcome. Otherwise, we will use either the two-sample t-test or Mann-Whitney U test as appropriate. The use of (log) transformations will be considered for time variables since these tend to be skewed. Binary secondary outcomes will be summarised using numbers/percentages and compared, where appropriate, using the χ^2^ test.

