#### Subgroup analyses

A subgroup analysis will be performed to investigate the effectiveness of the intervention based on the surgical specialty grouping:

Head and neck surgery, dental surgery, maxillofacial surgery.General surgery, orthopaedic surgery, other surgery.Urological surgery, gynaecological surgery.

In addition, a subgroup analysis will be performed to investigate the effectiveness of the intervention according to the age of the patient.

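### The primary model adjusts for specialty and centre but not for the child's age, a named risk factor known for every child, so some precision is left unused

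*Protocol article*

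**What the plan says.** Under Primary outcome analysis, mean m-YPAS-SF scores at time point 3 are compared "using a mixed-effects regression model with fixed effects for treatment and specialty, and a random effect for centre". No other term is listed. The specialty and centre terms correspond to the allocation method: "Randomisation will use minimisation to ensure balance across study sites and three groupings of surgical procedures". Age is not a minimisation factor.

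Age appears in four other places:
- The Introduction, on children's anxiety on the day of surgery: "Risk factors include the age of the child, personality traits such as low sociability and high impulsivity, parent anxiety".
- Inclusion criteria: "Children aged between 3 and 12 years of age on the date of parental consent to participate in the trial". Age is therefore recorded for every child and precedes treatment.
- Intervention: the app's reminders are timed differently for children aged 3 to 6 and for older children.
- Subgroup analyses: "a subgroup analysis will be performed to investigate the effectiveness of the intervention according to the age of the patient".

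The Sample size calculation section shows that the first target, 304, assumed adjustment for baseline m-YPAS-SF with a correlation of 0.7. The interim analysis found that correlation to be poor. The baseline score was then dropped and the target recalculated without it, at 596.

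For parents, Table 2 marks "VAS-Parent Anxiety" at T1 and T3. The Secondary outcome analysis section says that, in general, "for continuous secondary outcomes, we will perform analyses analogous to the analysis of the primary outcome".

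**The concern.** The design first relied on a strong prognostic covariate. When that covariate was withdrawn, the sample size was raised, but no other prognostic term entered the model. Age is the obvious candidate: the article itself ties it to the outcome, it is complete, it cannot be affected by allocation, and it spans a wide developmental range. Because age is in neither the minimisation nor the model, a chance difference in age between arms stays in the treatment estimate, and the outcome variance that age explains stays in the residual.

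The age subgroup analysis does not fill this gap. It asks whether the treatment effect differs by age; it does not adjust the main comparison.

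A second, conditional issue follows for parent anxiety. If the rule for continuous secondary outcomes is applied literally, T3 parent anxiety is analysed without its own T1 value, which would usually be its best predictor.

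**Working it through.** **Inputs from the article.** Difference 7.5 points, SD 26, 5% significance (taken as two-sided), 90% power, attrition 15%, 1:1 allocation, baseline correlation 0.7 (for the first target only).

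**Reproducing the stated sizes.**
- Per arm without covariates: 2 × [26 × (1.960 + 1.282) / 7.5]² = 252.55, so 253. Total 506; 506 / 0.85 = 595.3, so 596. This matches.
- Per arm with baseline adjustment: 252.55 × (1 − 0.7²) = 128.8, so 129. Total 258; 258 / 0.85 = 303.5, so 304. This matches.

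The move from 304 to 596 is therefore exactly the cost of losing the assumed baseline adjustment.

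**Effect of adding age.** If age explains a share R² of the outcome variance, the residual SD is 26 × √(1 − R²). Evaluable children per arm are 596 × 0.85 / 2 = 253.3. The article gives no R², so the values below are assumptions. The last column is the total that would have been needed for 90% power, after 15% attrition.

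| Assumed R² | SE ratio √(1 − R²) | Power for 7.5 points | Total needed |
|---|---|---|---|
| 0 | 1.000 | 90.1% | 596 |
| 0.02 | 0.990 | 90.7% | 584 |
| 0.05 | 0.975 | 91.5% | 565 |
| 0.10 | 0.949 | 92.8% | 537 |
| 0.15 | 0.922 | 94.1% | 506 |

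The 506 in the last row is a recruitment total; that it equals the evaluable number above is coincidence.

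**Chance imbalance in age.** The unadjusted SE is 26 × √(2 / 253) = 2.31 points. For a linear age effect, the part of the estimate due to age imbalance has an SD of 2.31 × √R²:
- R² = 0.05: 0.52 points; an imbalance at 1.96 SDs moves the estimate by 1.0.
- R² = 0.10: 0.73 points; 1.4.
- R² = 0.15: 0.90 points; 1.8.

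Against the 7.5-point target, the 1.96-SD shifts are about 13% to 23%.

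**Parent anxiety at T3.** Adjusting for T1 with correlation r multiplies the variance by 1 − r². The article gives no r. Assumed values of 0.3, 0.5 and 0.7 cut the variance by 9%, 25% and 49% (SE ratios 0.954, 0.866, 0.714).

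**The case against.** The strongest reply is that nothing here is an error. Randomisation makes the comparison valid without age, and the standard error already allows for chance imbalance. The design and the model agree, since 596 was calculated without covariates. The SD of 26 was also chosen over the smaller feasibility values of 15.6 and 7.4 to guard against low power. The gain from age is assumed, and the trial's own experience urges caution, because an expected correlation of 0.7 turned out to be poor. The change would also come late: follow-up finished in May 2024. All of this stands, and it limits the point to an improvement in precision.

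A reader might infer more than the article supports:
- That the model contains no patient-level predictor. It does: specialty belongs to each child's procedure.
- That the lost baseline adjustment was left uncompensated and the trial is underpowered. The larger sample size compensates for it in full.
- That T3 parent anxiety will certainly be analysed without its baseline. The article says only that secondary analyses are in general analogous, and covariates for single outcomes may be set in the statistical analysis plan, which is not shown.

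It is also uncertain whether T1 parent anxiety was still collected once consent could be remote. Table 2 still marks the T1 m-YPAS-SF that was dropped, so its T1 column may be out of date. The Other planned analyses section does list baseline parent anxiety, but it lists the child's alongside it.

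The reply does not remove the age point. The article states the model's terms explicitly, and its referral to the statistical analysis plan names missing data, non-compliers and withdrawals, not covariates.

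**Conclusion.** The point holds as a modest, nearly free improvement. The stated primary model omits age, which the article calls a risk factor and knows for every child. Under assumed R² of 2% to 15%, adding it is worth about 0.6 to 4 percentage points of power on a base of 90.1%, and it removes a possible shift of about 1 to 2 points from an unlucky age imbalance at R² of 5% to 15%. These figures rest on the article's SD and attrition and on an assumed R².

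The parent-anxiety part is conditional. It applies only if the T1 measure was collected before allocation was known. Where it applies, the gain could be larger than for age, but it too depends on a correlation the article does not report.

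**What to change.** Before unblinding:

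1. Add age at consent as a continuous fixed effect to the primary model, with a prespecified form that allows for non-linearity (a restricted cubic spline is one option). Carry it into the continuous secondary models built on the primary one.
2. Report the model now stated, with treatment, specialty and centre only, as a sensitivity analysis.
3. Confirm whether T1 parent anxiety was collected throughout and before allocation was known. If so, include it as a covariate in the T3 parent-anxiety model. If collection lapsed after the pause, say so; a covariate missing for most families would recover little.

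The age change costs a line or two of analysis-plan text and needs no new data. Its drawback is a late change to a prespecified primary model, so the amendment must be dated and documented as made before unblinding. If unblinding has already taken place, the stated model should stay primary and the age-adjusted result should be labelled supplementary.

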### Outcome measures

#### Primary outcome

The primary outcome is preoperative anxiety in the child undergoing surgery, assessed using the m-YPAS-SF, immediately before induction of anaesthesia. The m-YPAS-SF is a valid tool for the accurate measurement of paediatric perioperative anxiety, with good inter-rater and intrarater reliability.^26^ Children are scored in four categories: activity, vocalisations, emotional expressivity and state of apparent arousal, according to predetermined Likert scale observations. Each category score is divided by its highest possible score, before being added together; these scores are then divided by four and multiplied by 100, giving a value between 22.92 and 100. Higher values indicate greater anxiety levels, with scores greater than 30 typically representing clinically significant anxiety and those above 40 representing severe anxiety.^27^

To ensure high inter-rater reliability across all sites and over the whole trial recruitment period, we have created an e-learning module, modified from Jenkins *et al*’s proposed method.^26^ This provides assessor training and enables the testing of inter-rated reliability at multiple time points. For the training, trainee observers watch an introductory lecture outlining the creation of the mYPAS-SF, before observing and scoring 10 real-life case videos. After comparing their scores to five expert scorers, they can listen to explanations as to how and why each expert scored that case. Following this, the trainee observers undertake a test, scoring five new case videos. To pass, they must achieve a Kappa score of 0.7 in each of the four domains to be approved as a data collector.

All sites were required to provide at least two research staff who had passed the training before site opening was permitted; furthermore, after our trial pause because of the COVID-19 pandemic, all trial staff were required to repeat the end-of-training test and re-do the training if required to evidence their competence at undertaking the primary outcome assessment.

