### Sample size calculation

Local validation of the m-YPAS-SF scoring tool was performed at University College London Hospital. A total of 39 patients, requiring a general anaesthetic for day-case surgery, were observed in the anaesthetic room (time point 3). This showed that 67% of participants displayed significant anxiety on the day of surgery—defined as a m-YPAS-SF score of greater than 30, with a mean m-YPAS-SF score of 37.9 in the anaesthetic room (time point 3), similar to recent published literature^30 31^ and our feasibility trial results. These patients would represent the control arm in the RCT.

The original sample size of 304 patients was calculated to detect a 7.5-point difference in m-YPAS-SF scores between the control and intervention arms at the 5% significance level with 90% power. This assumed a common SD of 26, obtained by combining data assessing the results of mYPAS-SF scores of 3798 children.^26^ Use of this SD over the scores seen in the feasibility trial (15.6 and 7.4 in the standard care and intervention group respectively) was chosen to ensure that the study was not underpowered due to any variability in SD between sites. In addition, the sample size calculation was based on a primary analysis that was adjusted for baseline m-YPAS-SF score and assumed a correlation of 0.7 between the baseline and follow-up values. An attrition rate of 15% was also assumed.

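### The primary analysis allows the m-YPAS-SF to be transformed if residuals are not normal; the scale's floor makes that trigger near certain, and a transformed test could replace the 7.5-point mean difference that sizes the trial

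*Protocol article*

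**What the plan says.** In the protocol article, Primary outcome analysis, the comparison is defined on the original scale: "Our primary analysis will compare mean mYPAS-SF scores at time point 3". The model is a mixed-effects regression with treatment and specialty as fixed effects and centre as a random effect. The same paragraph then provides for a change of scale: "If substantial departures from normality occur, then transformations of the outcomes will be considered to achieve normality (of the residuals").

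Three other places bear on this:

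- Primary outcome: the score is built from four categories, "giving a value between 22.92 and 100".
- Sample size calculation: the original number was "calculated to detect a 7.5-point difference in m-YPAS-SF scores between the control and intervention arms", "at the 5% significance level with 90% power", with a planning SD of 26. The revised 596 drops only the baseline adjustment. The local validation sample of 39 children is reported "with a mean m-YPAS-SF score of 37.9 in the anaesthetic room (time point 3"), and "67% of participants displayed significant anxiety on the day of surgery", meaning a score above 30. The feasibility SDs were "15.6 and 7.4 in the standard care and intervention group respectively".
- Secondary outcome analysis: continuous secondary outcomes are in general to be handled in the same way as the primary.

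The article names no transformation and no threshold for a substantial departure. Those details may be in the statistical analysis plan, which is not shown, and their absence is not the point here. The point is the rule that the article does state.

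**The concern.** A residual check that may change the outcome scale is harmless if it is unlikely to be triggered, or if the changed analysis answers the same question. Neither seems to hold here. The mean lies close to a hard lower limit, so skewed residuals with children clustered at the floor are to be expected. A log or similar model also estimates something other than a difference in mean scores.

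At stake is which hypothesis the primary p-value tests. The trial is sized for 7.5 points on the original scale. A ratio of geometric means does not translate into one point difference and can differ from 1 when mean anxiety is the same in both arms. The scale would also be settled after the outcome data had been examined.

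**Working it through.** **1. The plan's own sample sizes.** Inputs: difference 7.5, SD 26, 5% level (two-sided assumed), 90% power, 15% attrition, 1:1 allocation.

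- Revised: n per arm = 2 × (1.960 + 1.282)² × 26² / 7.5² = 252.6, so 253. Total 506; 506 / 0.85 = 595.3, so 596.
- Original: multiply by 1 − 0.7² = 0.51, giving 128.8, so 129 per arm. Total 258; 258 / 0.85 = 303.5, so 304.

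Both stated figures are reproduced, and both rest on a raw-scale difference in means.

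**2. How close the floor is.** For a normal model, the share below the minimum is Φ((22.92 − mean) / SD). The intervention mean of 30.4 is 37.9 − 7.5, the design target and not an observed value.

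| Mean | SD | z | Share below 22.92 |
|---|---|---|---|
| 37.9 | 15.6 | −0.96 | 16.8% |
| 37.9 | 26 | −0.58 | 28.2% |
| 30.4 | 7.4 | −1.01 | 15.6% |
| 30.4 | 15.6 | −0.48 | 31.6% |
| 30.4 | 26 | −0.29 | 38.7% |

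The last row is notional. At a mean of 30.4 the largest SD possible on this scale is √((30.4 − 22.92) × (100 − 30.4)) = 22.8. None of these shares can occur, so normal residuals are not attainable under any row. The validation sample points the same way: if 67% score above 30, the other 33% lie between 22.92 and 30. With category maxima of 4, 6, 4 and 4 (an assumption, which reproduces the floor: (3 × 1/4 + 1/6) / 4 × 100 = 22.92), that interval holds only three attainable scores: 22.92, 27.08 and 29.17.

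**3. Whether a transformation would work.** Scores were simulated with 253 per arm, as a shifted gamma and as a scaled beta. Shapiro-Wilk rejected normality in 100% of trials on both the raw and the log scale. In the continuous gamma model, the power transform (score − 22.92)^0.27 did give nearly normal residuals (rejection 7.6%). Once scores were rounded to the attainable values, the same transform failed in 100% of trials.

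**4. Whether one is needed.** With equal means and 253 per arm, the raw-scale test rejected in about 4.4% to 5.8% of simulated trials despite the skew.

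**5. What a log-scale test would do.** True means are equal in every row, so each rejection is a false claim about mean anxiety.

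| SDs (control / intervention) | Raw test | Log test |
|---|---|---|
| 15.6 / 7.4 | about 5% | about 53–65% |
| 14 / 10 | about 5% | about 16–19% |
| 11.5 / 11.0 | about 5% | about 5–6% |
| 15.6 / 15.6 | about 5% | about 5% |

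Ranges reflect the choice of distribution, rounding and common mean (34 or 37.9). In the first row the geometric-mean ratio averaged about 1.06, so the intervention arm would look more anxious although mean anxiety was identical. With a true 7.5-point benefit, the ratio ran from 0.79 to 0.84 depending on the SDs, so no single ratio corresponds to 7.5 points.

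**Limit of the simulations.** The documents do not give the shape of the distribution. The scaled-beta model with mean 37.9 and SD 15.6 put 56% of children above 30, against the reported 67%. The rejection rates are therefore illustrations, not forecasts.

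**The case against.** A reader might infer that the outcome is going to be transformed and the 7.5-point comparison abandoned. The text does not say that. Transformation is only to be considered, the mean comparison comes first as the primary analysis, and a statistician could look at the residuals and stay on the raw scale without departing from the protocol. The floor makes the trigger near certain, not the switch.

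A reader might also take the 53% to 65% figure as the expected false-positive rate. It is not. It needs equal means together with the feasibility SDs, a pairing the article does not report. Relative to the floor the planning values are nearly proportional: (37.9 − 22.92) / 15.6 = 0.96 and (30.4 − 22.92) / 7.4 = 1.01. Much of the difference in spread could simply follow from a difference in means. Keeping those ratios at a common mean of 34 gives SDs of about 11.5 and 11.0, and the log test then rejects at about 5% to 6%. The inputs also come from different sources: 37.9 from the validation sample (which the article calls similar to its feasibility results), the SDs from the feasibility trial, and 30.4 from the design target.

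Two further points stand. The planned comparison of the numbers scoring above 30 is unaffected by any transformation. Masked analysts and arms labelled A and B limit direction-driven choice of scale.

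What does not stand is that these points remove the problem. Masking does not stop the primary quantity being chosen after the data are seen. An unseen analysis plan may tighten the rule, but the sentence in the article would still allow the switch.

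**Conclusion.** The point holds in a conditional form and should be fixed; it does not invalidate the design. The article permits a transformation that its own figures make near certain to come up for consideration, that is unlikely to achieve normality on a discrete scale with many children at the floor, and that is unnecessary at about 253 per arm. If adopted, it could move the primary test from the mean difference that gives 596 to a different quantity.

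The practical size depends on whether spread differs by arm beyond what the means explain: none with identical distributions, about 16% to 19% rejection at equal means with SDs 14 and 10, and 53% to 65% in the constructed worst case. These rates rest on assumed score shapes, assumed category maxima and a log transform, since the article names none. The closeness of the floor and the reproduction of 596 rest on the article's figures alone, apart from two-sided testing.

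**What to change.** Replace the transformation sentence in Primary outcome analysis with a fixed rule. The primary estimate is the adjusted difference in mean m-YPAS-SF at time point 3 on the original scale, whatever the residuals look like, with robust (sandwich) or bootstrap standard errors, or a model with arm-specific residual variances. Any log-scale, other transformed or ordinal (proportional-odds) model is a labelled sensitivity analysis and cannot replace the primary result. Apply the same rule to m-YPAS-SF at time point 2 and to the VAS outcomes analysed in the same way. Align the statistical analysis plan, and record the change before the arms are unmasked.

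The cost is one or two sentences and a standard software option. No further data are needed, and the sample size stays at 596 because it already rests on the raw-scale difference.
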